## Abstract

**Background:**

Hospital-treated deliberate self-harm (DSH) is common, costly and has high repetition rates. Since brief contact interventions (BCIs) may reduce the risk of DSH repetition, we aim to evaluate whether a SMS (Short Message Service) text message Intervention plus Treatment As Usual (TAU) compared to TAU alone will reduce hospital DSH re-presentation rates in Western Sydney public hospitals in Australia.

**Methods/design:**

Our study is a 24-month randomized controlled trial (RCT). Adult patients who present with DSH to hospital emergency, psychiatric, and mental health triage and assessment departments will be randomly assigned to an Intervention condition plus TAU receiving nine SMS text messages at 1, 2, 3, 4, 5, 6, 8, 10 and 12-months post-discharge. Each message will contain telephone numbers for two mental health crises support tele-services. Primary outcomes will be the difference in the number of DSH re-presentations, and the time to first re-presentation, within 12-months of discharge.

**Discussion:**

This study protocol describes the design and implementation of an RCT using SMS text messages, which aim to reduce hospital re-presentation rates for DSH. Positive study findings would support the translation of an SMS-aftercare protocol into mental health services at minimal expense.

**Trial registration and ethics approval:**

This trial has been registered with the Australian and New Zealand Clinical Trials Registry (Trial registration: ACTRN12617000607370. Registered 28 April 2017) and has been approved by two Local Health Districts (LHDs). Western Sydney LHD Human Research Ethics Committee approved the study for Westmead Hospital and Blacktown Hospital (Protocol: HREC/16/WMEAD/336). Nepean Blue Mountains LHD Research Governance Office approved the study for Nepean Hospital (SSA/16/Nepean/170).

## Background

Hospital-treated DSH is common [1] and costly [2]. Repetition of DSH within 1 year of hospital admission occurs at a median proportion of 15% (interquartile range 12–25%) [1].

DSH is associated with a range of psychiatric issues [3], an increased risk of suicide attempts, and suicide [3, 4]. In Australia, DSH accounted for 6% of all hospitalised injury cases during 2012–2013 and four-billion dollars in healthcare expenditure annually, making prevention and early intervention an Australian national health priority [5]. Hospital-treated DSH predominantly includes deliberate self-poisoning (DSP) (approximately 90% of DSH cases) and other various methods, including, cutting, hanging, jumping, and burning [1]. Hospital-treated DSH is associated with an increased risk of suicide death, highlighting the importance of effective prevention and early intervention strategies.

BCIs, such as follow-up postcards, supportive letters, or phone calls have previously been shown to be associated with reductions in hospital re-presentation event rates. A recent systematic review and meta-analysis of BCIs for reducing DSH (letters, telephone calls and crisis “green cards”) found a non-significant benefit for any episode of repeat DSH (binary outcome) and a significant benefit for repetition event rates [6]. The individual studies identified in the systematic review and meta-analysis generally lacked statistical power and varied considerably in intervention timeframes and methodologies, highlighting the need for well-designed, large, RCTs to determine the efficacy of these BCIs.

SMS text messaging provides more immediate communication and may be a more effective intervention than postcards [6, 7]. Text messaging has been associated with positive outcomes for hospital patients in a pilot study [8] and in a prospective study [9]. These studies demonstrated the technical feasibility and acceptability of text messaging outreach in post-acute suicide attempters in different cultural contexts. Most participants considered the text message contacts an acceptable and useful form of help and indicated they wished to continue receiving those text messages.

If an SMS text messaging follow-up intervention is found to be effective in reducing DSH re-presentations, it would provide a lower-cost, higher coverage medical follow-up system than what has previously existed for this population.

## Methods/design

### Aims and hypotheses

The aim of this study is to investigate whether Treatment As Usual (TAU) aftercare for DSH patients plus supportive SMS text messages delivered over 1 year reduce DSH re-presentations to hospital, compared to TAU alone. Our hypotheses are: 1) SMS text messages *plus* TAU will be associated with a significantly lower incidence event rate of hospital DSH re-presentations, compared to the patient group receiving TAU; and 2) SMS text messages *plus* TAU will be associated with a significantly greater time to first hospital DSH re-presentation compared to TAU.

### Study design

A RCT will be conducted in three selected public hospitals in Western Sydney, Australia, and will have a 24-month recruitment period and a 12-month follow-up period. The study protocol is like the methodology employed in an earlier study [10], which was a two-year French multicenter RCT, comprising of DSH patients, similar text messages, and an SMS outreach schedule of 48 h, 7 days, 15 days and, then monthly for 12-months. Our study consists of a parallel design that will compare a control group (TAU condition) with patients who receive an Intervention condition (i.e. SMS text messages *plus* TAU). Outcome data on DSH will be obtained from routinely collected hospital records, extracted by trained research staff.

### Setting

Our study will be conducted at three large, public hospitals in Western Sydney; Nepean, Blacktown and Westmead Hospitals.

### Participants/Subjects

For the purpose of this study, participants will be defined as patients who have randomly been allocated to the Intervention condition and provide their informed consent to receive text messages. Subjects will be defined as patients who are randomly allocated to the TAU condition and do not receive text messages. To be eligible for study inclusion, patients must be: assessed at an emergency department (ED) after presenting with DSH; at least 16-years old; competent in reading and understanding English; and have a mobile phone. Patients will be excluded from the study if they: refuse to participate; do not have a mobile phone; do not have a fixed Australian address or are otherwise unable to provide informed consent.

### Randomization, allocation, and materials

Participants/subjects will be stratified (first ever hospital-treated DSH verses any subsequent episode), then randomly assigned and enrolled into the study following the Zelen single-consent design [11]. Since there are different repetition rates of DSH for initial and subsequent DSH, participant/subject numbers will initially be stratified by first or subsequent DSH presentation. They will then be randomized within strata, using random permuted blocks of size 6, to either the Intervention or control condition (TAU) using a computer-generated randomization program.

Study materials, including an ‘Allocation Information Sheet,’ will be organized within numbered envelopes, with each hospital having at least two ‘enrolment boxes’ (document drawers) containing a full set of materials. Research staff will confirm that the placement of research materials and the Allocation Information Sheets within envelopes match the randomized numbers generated from the randomization program (to prevent any tampering with the allocation sequence).

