### Procedure

The usual treating health and mental health clinicians (Psychiatrists, Clinical Nurse Consultants, Registered Nurses and Psychiatry Registrars) will assess patients at EDs, Toxicology Centers, Psychiatric Emergency Care Centers, and Mental Health Triage and Assessment Centers. Clinicians will enroll eligible patients into the Intervention or TAU conditions and record the name, Medical Record Number, mobile phone number and date of birth of participants/subjects on Allocation Information Sheets. Envelopes will be supplied at study commencement, including at least 500 green envelopes (numbered for first DSH presentation) and at least 500 blue envelopes (numbered for subsequent DSH presentation). Allocation Information Sheets will be concealed inside sealed envelopes and the allocating clinician will draw the next numbered envelope for each participant/subject form the appropriate stratification. Demographic information will be collected by hospital administration staff when patients first present to the ED.

Figure 1 outlines the methodological process that will be followed for the SMS SOS Study. Allocation will occur via numbered sealed envelopes. Upon enrolling patients into the study, health professionals will attach a patient identification label (which includes the patient’s name, gender, date of birth and Medical Record Number) to an Allocation Information Sheet, which would be drawn from a selected envelope. For patients allocated to the Intervention condition, clinicians will explain that they may receive text messages for up to 12-months post discharge. Clinicians will provide patients in the Intervention condition with a Participant Information Sheet and they will obtain written consent. To reduce unnecessary patient burden, patients allocated to the control condition (TAU) will not be recruited by clinicians, as per the Zelen single-consent design [11].

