### Sample size calculation

Assuming an incidence rate ratio (based on event rates) of RR = 0.66 [13] for the Intervention condition compared to TAU, with a 5% significance level, 80% power, and 10% adjustment for correlation of individuals within hospitals, a total sample size of 796 participants/subjects is required (398 participants in the Intervention condition and 398 subjects in the control condition). We have also assumed a median survival time (time to first repetition) in the TAU condition of 4.3 years. Currently ~ 15% in the usual care group who present for DSH re-present within the following 12-months, or a probability of survival of 0.85. Median survival (m) after 1-year (t) in the usual care group is t*log_e_(1/2)log_e_(*p* = 4.3 years). For assessing differences in median time to first repetition, assuming a median survival time in the usual care group of 73.5 days [12] and a similar relative difference in event rates between Intervention and TAU conditions as above (RR = 0.66), [13] the estimated median survival time in the Intervention condition is 121.8 days, which requires a total sample size of 138 participants/subjects (69 participants in the Intervention condition and 69 subjects in the TAU condition), with 5% significance and 80% power, and 10% adjustment for correlation of individuals within hospitals. The number of patients likely to die within the study period is very small. A previous longitudinal study in a similar Australian hospital setting [12] found a 1% suicide rate after 24 months and nearly a 2% suicide rate after 5 years.

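### Treating clinicians draw envelopes from fixed blocks of six and, as described, label the sheet only after opening, so allocation could be foreseen in part or swapped without detection

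*Protocol article*

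**What the plan says.** All references are to the Protocol article.

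- **Sequence (Randomization, allocation, and materials).** Patients are "stratified by first or subsequent DSH presentation" and then allocated "using random permuted blocks of size 6, to either the Intervention or control condition (TAU". Only one block size is given. No ratio is stated, but the Sample size calculation section plans "398 participants in the Intervention condition and 398 subjects in the control condition", which implies three and three per block.
- **Storage (same section).** Envelopes are kept on site, with "each hospital having at least two ‘enrolment boxes’ (document drawers) containing a full set of materials". The article does not say how the numbers are divided among drawers.
- **Who allocates (Procedure).** "Clinicians will enroll eligible patients into the Intervention or TAU conditions", and "the allocating clinician will draw the next numbered envelope for each participant/subject" from the relevant stratum. These are the usual treating staff. They explain the messages and take written consent in the Intervention arm, and do not approach the control arm.
- **When identity is attached (Procedure).** The patient label is fixed "to an Allocation Information Sheet, which would be drawn from a selected envelope".
- **Safeguards.** Envelopes are sealed and numbered and must be taken in order. Research staff also check that the contents match the generated list.

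**The concern.** Concealment has to do two things: keep the next allocation unknown while the patient is being considered, and make the allocation irrevocable once it is seen. The procedure as written is weak on both.

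**Reversibility.** The sheet is inside the sealed envelope and the label goes on the sheet. On the stated steps, the clinician therefore sees the allocation before any identifier is tied to that envelope. A sheet could be set aside and another drawn. This needs no knowledge of the block size.

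**Predictability.** With one fixed block size in an open trial, a person who follows a sequence can sometimes know the next allocation.

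The exposure matters here because the same clinician applies eligibility criteria that involve judgement (competence in English, ability to consent) and then has extra work in one arm only. If foreknowledge or swapping affects who is enrolled or where, the arms differ at baseline. Intention-to-treat analysis cannot restore patients who were never enrolled, and the planned confounder adjustment cannot remove differences in unmeasured characteristics.

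**Working it through.** The article gives no predictability figure, so there is none to reproduce.

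**Inputs.** Block size 6 and two strata (Randomization, allocation, and materials); 3 + 3 per block, inferred from the equal arms of 398 (Sample size calculation).

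**1. Allocations known with certainty.** There are C(6,3) = 20 equally likely blocks. An allocation is determined when one arm's three places are already used up.

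| Position in block | P(already determined) | P(best guess correct) |
|---|---|---|
| 1 | 0 | 0.50 |
| 2 | 0 | 3/5 = 0.60 |
| 3 | 0 | 0.4 × 3/4 + 0.6 × 1/2 = 0.60 |
| 4 | 2/20 = 0.10 | 0.1 × 1 + 0.9 × 2/3 = 0.70 |
| 5 | 8/20 = 0.40 | 0.4 × 1 + 0.6 × 1/2 = 0.70 |
| 6 | 1.00 | 1.00 |
| Sum | 1.5 | 4.1 |

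- Certain: 1.5 / 6 = 25.0%. As a check, the expected final run in a block of 2m is 2m/(m + 1), which is 6/4 = 1.5 for m = 3.
- Best guess, choosing the arm with more places left: 4.1 / 6 = 68.3%, against 50% with no information.

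Both figures assume an observer who knows the block size and has seen every preceding allocation in that sequence.

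**2. Effect of varying the block size.** This was simulated for an observer who knows the set of possible sizes but not where blocks begin. The sizes are assumptions for illustration.

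| Block sizes | Certain | Best guess correct |
|---|---|---|
| 6 only | 25.0% | 68.3% |
| 4 and 6 | 5.6% | 69.1% |
| 4, 6 and 8 | 2.2% | 67.8% |

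Varying the size removes most of the certainty and leaves guessing almost unchanged.

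**3. Swapping.** No arithmetic applies; the stated steps are set side by side. The sheet is sealed in a numbered envelope; the clinician takes the next number; the label is put on the sheet drawn from it. The staff check compares contents with the list. A correctly filled envelope used for the wrong patient, or out of order, still matches the list, so that check cannot reveal a swap.

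**The case against.** **The percentages are ceilings.** This stands. Enrolment is by psychiatrists, registrars and several grades of nurse, in several kinds of department at three hospitals, with at least two drawers in each. Few people would see every allocation in a sequence, and nothing says that enrolling staff are told the block size. How numbers are split among drawers is not stated either; if one series is spread over several drawers, following one drawer reveals less. A reader might infer that one in four allocations in the trial, 0.25 × 796 = 199, would be known in advance. The documents do not support that count.

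**A swap would break a written rule.** This also stands. The next-number rule forbids it, and nothing shows that it would happen. The point is only that no stated step prevents or detects it.

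**The full procedure may record more.** This stands in part. The enrolment flowchart (Fig. 2) is not shown, and envelopes may be marked or logged before opening. The Procedure section nevertheless describes the labelling step in words, and places the label on the sheet drawn from the envelope. The weakness therefore lies in a step that is stated.

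**The direction of bias is unknown.** This stands. It is tempting to infer that clinicians would steer harder-to-engage patients to TAU to avoid consent work. They might equally steer patients who worry them towards the messages. The documents support neither.

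**Conclusion.** The concealment procedure, as described, has a real and correctable weakness. The firmer part is reversibility: no stated step ties a patient to an envelope before the allocation is seen, and the stated content check would miss a swap. That rests on the labelling order in the Procedure section and would fall away if the full protocol records identity on the sealed envelope.

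Predictability is secondary. Up to 25% of allocations are certain, and up to 68% correctly guessed, within a sequence that one person has followed completely while knowing the block size. These figures assume 3 + 3 blocks. The actual extent, and the size and direction of any effect on the treatment comparison, cannot be derived from the documents. The change is worth making because it is cheap and because analysis cannot repair a failure of concealment.

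**What to change.** 1. **Main remedy.** Before opening, write the patient identifier, date and time on the outside of the sealed envelope, and count the patient as randomised from that point. Put this step in the enrolment flowchart.
2. **Monitoring.** During the trial, reconcile envelope numbers against these times within each series, so that skipped, out-of-order or missing envelopes show up.
3. **Unused envelopes.** Re-generate the remaining sequence with randomly varying block sizes that are not disclosed to sites. With assumed sizes 4, 6 and 8, certainty falls from 25% to about 2%, but the best-guess rate stays near 68%, so this supplements step 1 and does not replace it.

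Steps 1 and 2 close the swap route. They do not stop a clinician with a guess about the next envelope from not enrolling a patient at all; step 3 reduces that only where the guess would have been a certainty.

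**Cost.** One extra line in the flowchart, routine reconciliation by research staff, and some re-packing. The re-packing depends on how many envelopes remain: at least 500 per stratum are supplied at commencement. Varying block sizes also permit a slightly larger imbalance within a stratum.

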### Data collection

Clinical and demographic information of patients will be recorded, including: presenting group (i.e. first DSH or subsequent DSH presentation) randomized condition (i.e. TAU or Intervention); mobile phone number; hospital of study enrollment; key dates (admission, enrollment, discharge, and deceased dates); clinical diagnoses; primary DSH method; gender, birth date, place of residence, marital status, primary language spoken, Australian Aboriginality status, and ethnicity), Medical Record Number, first name, and last name.

### Procedure

The usual treating health and mental health clinicians (Psychiatrists, Clinical Nurse Consultants, Registered Nurses and Psychiatry Registrars) will assess patients at EDs, Toxicology Centers, Psychiatric Emergency Care Centers, and Mental Health Triage and Assessment Centers. Clinicians will enroll eligible patients into the Intervention or TAU conditions and record the name, Medical Record Number, mobile phone number and date of birth of participants/subjects on Allocation Information Sheets. Envelopes will be supplied at study commencement, including at least 500 green envelopes (numbered for first DSH presentation) and at least 500 blue envelopes (numbered for subsequent DSH presentation). Allocation Information Sheets will be concealed inside sealed envelopes and the allocating clinician will draw the next numbered envelope for each participant/subject form the appropriate stratification. Demographic information will be collected by hospital administration staff when patients first present to the ED.

Figure 1 outlines the methodological process that will be followed for the SMS SOS Study. Allocation will occur via numbered sealed envelopes. Upon enrolling patients into the study, health professionals will attach a patient identification label (which includes the patient’s name, gender, date of birth and Medical Record Number) to an Allocation Information Sheet, which would be drawn from a selected envelope. For patients allocated to the Intervention condition, clinicians will explain that they may receive text messages for up to 12-months post discharge. Clinicians will provide patients in the Intervention condition with a Participant Information Sheet and they will obtain written consent. To reduce unnecessary patient burden, patients allocated to the control condition (TAU) will not be recruited by clinicians, as per the Zelen single-consent design [11].

**Fig. 1 Fig1:**
[figure not shown]
RCT design flowchart

To reduce the chance of patients being re-enrolled into the study, treating clinicians will review an Enrolled Patients List and a Patient Exclusion List placed in a folder above each enrollment box to be checked before recruitment. A hardcopy of the Enrolled Patients List and the Patient Exclusion List will be used due to the limited capacity of the patient electronic medical record system to reliably identify (‘flag’) to clinicians those patients who have previously been enrolled into the study. The folder will also contain an Enrollment Procedure Flowchart (Fig. 2) regarding the enrollment process and the definition of DSH used for the study.

**Fig. 2 Fig2:**
[figure not shown]
Enrolment procedure flowchart

### Intervention

Patients in the Intervention condition will receive TAU *plus* a series of supportive SMS text messages. The Intervention condition will consist of nine text messages in total, which were developed based on feedback received from a panel of lived experience mental health consultants. Seven people with mental health problems and/or a history of DSH informed the development of the text messages. According to the feedback received, each text message was clear and easy to read, and suited the purpose of making brief contact and offering support phone numbers.

The text messages will be personalized with the names of patients and will be sent with identical outreach schedules. Nine automated text messages will be sent to patients assigned to the Intervention condition at months 1, 2, 3, 4, 5, 6, 8, 10, and 12 post-discharge. This is like the contact schedule employed in the Postcards from the Edge study [12]. There will be three different SMS text messages sent to participants, which express concern for their wellbeing and encourage them to telephone clinical crises and mental health support services, including Lifeline and NSW Health’s ‘Mental Health Line,’ if needed. Patients in the Intervention condition will be advised once in the first text message that they will not be able to directly reply to text messages. The three text messages sent to patients in the Intervention condition are as follows:

Text message 1.
*Dear [name].*

*We hope that things have been going well for you since we last had contact.*

*Just a reminder that the 24-h contact line ([name]) is there if you’d like to connect with someone and Helpline staff ([name]) can put you in touch with your local health service if needed.*

*Best wishes. [Return SMS messages are unavailable from this service.]*

Text message 2.
*Hi [name].*

*We hope that you’ve been ok since our last contact. We’re just checking in with you.*

*A 24-h phone line is there for you in case you’d like to connect with someone ([name]) or to contact your local health service ([name]).*

*Best wishes.*

Text message 3.
*Dear [name].*

*Just checking in with you.*

*A reminder that help is there if you need it. Just call ([name]) or ([name]) for support.*

*Best wishes.*

The SMS text messages will be scheduled for automatic distribution via a private and as secure as possible medium, considering available Australian telecommunications providers. The telecommunications provider was selected based on its capacity to provide both an automated service with message variants and to personalize messages with the names of specific recipients. These features will support large scale, low cost delivery of a future mental health aftercare service for this population. The three SMS text messages will be delivered to participants according to the schedule detailed in Table 1.

**Table 1 Tab1:** Delivery schedule for the three supportive SMS text messages

Text message	Month/s to be delivered
1	1 only
2	2, 4, 6 and 10
3	3, 5, 8 and 12

